## Abstract

**Background:**

Hypertension is the premier modifiable risk factor for recurrent stroke. In sub-Saharan Africa (SSA) where the stroke burden is escalating, little is known about the role of behavioral interventions in enhancing blood pressure (BP) control after stroke.

Our objective is to test whether an m-Health technology-enabled, nurse-led, multilevel integrated approach is effective in improving BP control among Ghanaian stroke patients within 1 month of symptom onset compared with standard of care.

**Methods:**

This two-arm cluster randomized controlled feasibility pilot trial will involve 60 recent-stroke survivors. Using a computer-generated sequence, patients will be randomly allocated into four clusters of 15 patients each per physician: two clusters in the intervention arm and two in the control arm. Patients in the intervention arm will receive a simple pillbox, a Blue-toothed UA-767Plus BT BP device and smartphone for monitoring and reporting BP measurements and medication intake under nurse guidance for 3 months. Tailored motivational text messages will be delivered based upon levels of adherence to the medication intake. Both groups will be followed up for 6 months to compare BP control at months 3, 6 and 9 as primary outcome measure. Physicians assessing BP control will be blinded to arms into which patients are allocated. Secondary outcome measures will include medication adherence scores and Competence and Autonomous Self-regulation Scale scores. A qualitative study is planned after follow-up to explore the lived experiences of participants in the intervention arm.

**Discussion:**

A feasible and preliminarily effective intervention would lead to a larger more definitive efficacy/effectiveness randomized controlled trial powered to look at clinical events, with the potential to reduce stroke-related morbidity and mortality in a low- to middle-income country.

**Trial registration:**

ClinicalTrials.gov Identifier: NCT02568137, registered on 13 July 2015.

**Electronic supplementary material:**

The online version of this article (doi:10.1186/s13063-016-1557-0) contains supplementary material, which is available to authorized users.

## Background

Hypertension (HTN) is the premier modifiable risk factor for recurrent stroke [1]. Fortunately, with control of HTN [2], recurrence of and mortality from stroke can be greatly reduced [3–5] as has been seen in several high-income countries (HICs) [6–9]. However, for low- and middle- income countries (LMICs) that disproportionately bear the global burden of stroke, these gains have not materialized [10]. Data from the Global Burden of Disease 2013 study suggest that deaths and disability-adjusted life years from stroke in LMICs account for 75.2 % and 81.0 % of global estimates, respectively [11].

Achieving and sustaining blood pressure (BP) control is a global challenge [12] particularly in LMICs including sub-Saharan Africa (SSA) [12–14]. A multinational survey has identified that 46.5 % of participants with HTN were aware of the diagnosis and 32.5 % of hypertensive participants had their BP controlled, with rates of awareness and control of BP significantly higher in HICs compared with LMICs [12]. Key factors responsible for uncontrolled HTN are medication non-adherence and failure to intensify therapy in a timely manner (i.e., therapeutic inertia) [15, 16]. Furthermore, the lack of availability, poor affordability and low rates of utilization of secondary prevention cardiovascular medicines in LMICs [17, 18] combined with low literacy levels, traditional beliefs and misconceptions about HTN may all contribute to the low prevalence of HTN awareness, treatment and control which poses a serious threat to stroke prevention.

Systematic reviews of randomized controlled trials (RCTs) involving uncontrolled hypertensive patients have indicated that BP self-monitoring, medication-reminding tactics and the use of case managers each improve adherence, therapeutic inertia and BP levels [19–22]. No RCTs looking at medication adherence or BP self-monitoring have been designed specifically for people in SSA, especially for those at high risk for future stroke. However, mobile health (m-Health) technology offers a promising approach to address this need [23–30]. Most adults in SSA own a cell phone (approximately 73 %) [31, 32], smartphone ownership is burgeoning (approximately 35 %) [33], and m-Health has produced promising results in chronic disease management (e.g., HIV) in SSA [34–36].

An iterative, theory-guided, design process was used by our group to develop an m-Health BP self-management control program for poor, rurally located Hispanic and African American hypertensive patients called the Smartphone Med Adherence Stops Hypertension: SMASH) [37, 38]. SMASH included multilevel components:Patient-level interventions included: (1) sequential automated reminder signals, (2) tailored Short Message Service (SMS)/voice mail motivational and reinforcement messages based upon adherence to daily medication adherence and BP monitoring (every 3 days); and provider-level interventions entailing: (a) emailed summary reports with stepped care guidelines attached every 2 weeks, (b) phone alerts to clinic nurse navigator when verified out-of-range BP measurements occur. Several 3- and 6-month pilot RCTs were conducted with Hispanics and African Americans with uncontrolled HTN. In each RCT, we observed high acceptability, self-efficacy for following a medical regimen, 95–100 % medication adherence, a mean of 95 % achieving guideline-designated BP control compared to an average of 18 % in standard care (SC) patients and large systolic blood pressure (SBP) reductions (mean: -32 mmHg) [39, 40]. SMASH is capable of adaptation to other poor, undereducated patients with HTN using an iterative patient/provider-centered design approach.

The Phone-based Intervention under Nurse Guidance after Stroke (PINGS) study is fashioned after the SMASH program. The objective of the PINGS study is to test whether a theoretical-model-based, m-Health technology-enabled, multilevel integrated approach is feasible in improving sustained BP control among 60 recent Ghanaian stroke patients within 1 month of their stroke, while building capacity in Ghana for longer-term testing of m-Health technology for chronic disease management in this resource-limited setting. A nurse navigator will be employed in the study design as a task-shifting strategy in the care of chronic diseases in SSA where there is a perennial paucity of neurologists and physicians [41].

## Methods

### Trial design

This is a two-arm cluster randomized controlled trial involving 60 stroke survivors with the physician as unit of randomization and patients as unit of analysis. Each of the four physicians will be recruited and randomly assigned to the intervention or control group by the statistician (who is not involved in provider or patient recruitment nor data collection) using a computer-generated random sequence. Four groups/clusters of 15 eligible patients will be assigned to either control or intervention arms by the study coordinator after having met study criteria for enrollment (Fig. 1). A cluster randomized trial has been chosen to avoid potential treatment contamination in which physicians might unintentionally provide patients with different degrees of attention or blending of treatment protocols. The checklist for the study protocol is provided as Additional file 1.

**Fig. 1 Fig1:**
[figure not shown]
Phone-based Intervention under Nurse Guidance after Stroke (PINGS) study algorithm

### Study setting

This study will be conducted at the Neurology Clinic in Komfo Anokye Teaching Hospital, a tertiary referral center in Kumasi, Ghana [42].

### Study participants

The participants will be 60 adult Ghanaian recent-stroke patients (within 1 month of stroke onset) with uncontrolled HTN who meet the inclusion/exclusion criteria. SBP ≥140 mmHg is used as the selection variable since most patients with HTN who are aged below 65 years have systolic or combination systolic/diastolic hypertension and, for the majority, controlling SBP results in diastolic blood pressure (DBP) also being controlled [43, 44].

### Inclusion criteria

Above the age of 18 years; male or femaleA stroke diagnosis no longer than 1 month before enrollmentHave uncontrolled HTN (SBP ≥140 mmHg) based upon last pre-stroke inpatient or outpatient encounter clinic within the previous 12 months, as well as post-stroke encounter and at the screening/recruitment visitMust be legally competentMust own or have a close home-sharing family member with a cell phone

### Exclusion criteria

Failure to meet any of the inclusion criteriaSevere cognitive impairment/dementia (Modified Mini-Mental State Examination (MMSE) score ≤24)*Severe global disability (modified Rankin Scale (mRS) score ≥3)*Renal dialysis; awaiting renal transplant or transplant recipientCancer diagnosis or treatment in the past 2 yearsPlanned pregnancyVulnerable populations, such as pregnant or nursing women, prisoners and institutionalized individuals**MMSE score ≤24 and global disability (mRS) score ≥3 excludes patients who have severe cognitive impairments and medical limitations that would interfere with adequate participation in the PINGS project*.

### The intervention

#### Patient level

Patients in the intervention group will be given an inexpensive simple pillbox and loaned a Blue-toothed UA-767Plus BT BP device along with a medical regimen assistance application for their smartphone for automatic relay of BP data to a central server at the Medical University of South Carolina. Patients needing a loaner 2 or 3G phone will receive one. The PINGS nurse navigator and patient will establish times that antihypertensive medications and other medications such as antiplatelet agents, statins and oral hypoglycemic agents will be taken daily for entry into the application. The patient (and caregiver) will show that they can properly load the pill tray, view the BP protocol demonstration video and successfully take three consecutive BP measurements using the app’s protocol, and view the feedback chart and/or see their immediate BP data from that session on their phone.

They will receive written and oral information on adherence criteria:To take their medications within 2 hours of designated times,To take their BP every 3 days in the morning and evening

A list of motivational and reinforcement messages will be developed by adapting ones used in earlier m-Health BP control studies [38–40] and enhancing them guided by self-determination theory constructs of competence and autonomous self-regulation [45, 46]. These tailored brief SMS messages will be based on the previous day’s reported medication adherence levels. After two consecutive weeks of 100 % adherence (i.e., medication intake reports using established algorithms based upon proximity to preestablished times for pill intake, using time stamps of when doses were taken, sent via phone) and verification with Medication Possession Ratios (MPRs), the schedule of SMS message delivery will switch to a variable interval schedule [38, 47]. Messages will be tapered to several times per week on a 3-day average variable interval schedule unless adherence drops to below 90 %.

Patients will receive a SMS reminder message on the morning that they are to take their BP measurements. They will receive a tailored SMS message reinforcing their having taken their BP measurements the day after doing so. After each BP session, patients will receive visual BP feedback on their phone, and can select charts showing cumulative averages across weeks/months compared to BP control threshold lines. Patients will also receive lifestyle tips via SMS.

After completion of the 3-month trial, patients will return the BP monitors (and smartphones). Those who experience delayed monthly refill (more than 3 days from the designated time) or uncontrolled BP or a missed appointment on two occasions at the standard 3-month clinic visit will be called by the nurse navigator. The nurse navigator will be trained to conduct motivational interviewing to help these patients identify barriers/issues and develop an action plan. This may include a patient restarting some PINGS’ components (e.g., medication intake reminder alert via SMS delivery system reactivation, motivational messages), being referred for additional help (e.g., mental health), and so forth.

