### Control arm/standard of care

Inclusion criteria include owning a cell phone with at least SMS and voice mail. To control for attention exposure, they will receive SMS messages dealing with healthy lifestyle behaviors (smoking, diet, physical activity) but not with medication adherence, hypertension- or stroke-related issues. Messages will be of the same frequency and size as those in the intervention arm. Every 3 days (comparable to those in the intervention arm) they will receive lifestyle messages and if they have a smartphone, the SMS messages will have either PDFs attached or weblinks to a brief video clip or series of charts, information, and so forth. This information will be sent in two messages and requires 3–5 min per message to view or listen to (similar to the BP protocol duration). All four physicians will receive the expert consensus guideline charts. Intervention tactics will cease for both groups after the 3-month trial.

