### Follow-up phase

Subjects in both arms of the study will be followed up for 6 months after the initial 3-month trial. During the follow-up period, subjects will attend clinics monthly where their physicians will assess them clinically. At months 3, 6 and 9 post enrollment patients and providers will undergo assessments on methodological parameters and consumer responses, clinic BP measurements, medication adherence, health literacy on stroke and HTN as well as self-determination theory constructs such as Autonomous Self-regulation and Competence Scales. Physicians in both groups will also undergo assessment on adherence to BP management protocols (Fig. 1 and Table 1).

**Table 1 Tab1:** Study outcome measures

Outcomes	Psychometrics (internal consistency [α], test-retest reliability [r]) NOTE A^a^	Time points
Primary outcomes		
Feasibility: methodological parameters and consumer responses	Recruitment and retention rates; Self-report: Patient/Provider Satisfaction Scale (.82–.96, test-retest (1 week) .98) [74, 75], fidelity checklists: patient level (e.g., connection; BP uploads via phone; opening of messages/educational information and provider level (e.g., delivery of provider summaries; phone alerts)	Baseline, 3, 6, 9 months
Clinic: BP	Clinic-based BP	
Feedback and refinement	Focus groups	Providers and IG: 9 months
Secondary outcomes		
Medication adherence Physician adherence	Medication Possession Ratio (MPR); Morisky Medication Adherence Scale (α = .76–.83, r = .64) [76, 77], provider guideline adherence: timely med changes (date of script changes following BP feedback (bi-monthly PINGS reports/clinic BPs)	Baseline, 3, 6, 9 months
Self-determination theory constructs	Autonomous Self-Regulation (α = .81–.84, r = .38) [78], Competence Scale (α = .88–.95, r = .32–.46) [51, 52, 78].	
Potential moderators/mediators		
Demographics	Age, education level, income	Baseline
HTN/stroke knowledge, health literacy, anthropometrics	Self-report: HTN/stroke knowledge (.70) [54, 55], health literacy (r = .74, .82) [78–80], Height/ weight/girth	Baseline, 3, 6, 9 months
Medication adherence factors	Side effects, adverse events	As reported, and 3, 6, 9 months

^a^Basic psychometric property analyses (e.g., internal consistency, test-retest reliability) will be conducted during first 3 months on scales, which have not been used with Ghanaian stroke patients

*BP* blood pressure, *HTN* hypertension, *IG* Intervention Group

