#### Primary outcome measures

For these measures, generalized linear mixed models (GLMM) will be used to compare the two groups with group as primary independent variable and percent success reaching BP control (or resting BP changes individually) as the primary dependent variable (Table 2) [64]. GLMM allow for missing data, measurement at different times and take into account the effect of clustering, i.e., correlation of repeated measurements within patients clustered within MD (Medical Doctor) provider. Group and time (baseline, 3, 6 and 9 months) will be fixed effects; demographics and secondary outcome measures (e.g., medication adherence via the MPR) will be adjustment covariates. We will assess changes over time via a time-by-intervention interaction term in multivariable models. We will estimate differences (for means or proportions) in ancillary moderator and mediator measures between the two groups via 95 % CIs as appropriate (e.g., self-efficacy, autonomous regulation, and so forth.). We will estimate differences (via 95 % CI) in proportions and average slopes between intervention versus control groups and evaluate linearity of trajectories as input for future RCT analysis strategy. We will estimate percent success reaching BP control for each subject over the trial (baseline, 3, 6 and 9 months), and the within-subject longitudinal trajectories (e.g., slopes), and then summarize as mean longitudinal trajectory within each treatment group (e.g., mean slopes with 95 % CI). Intracluster correlation coefficient (ICC) and variance estimates will be obtained of efficacy outcomes and covariance structure of the longitudinal scores for determination of sample size (and hence adequate power) for a future RCT. Multiple imputation methods will be used for missing end-of-study outcomes. Dropout rate, both selective and differential, is an important issue. If more than 10 % of data are missing, we will add an intermediate evaluation point in a future RCT to provide more data for use in endpoint imputation.

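### The protocol both ends the intervention at month 3 and allows parts of it to restart afterwards in one arm, so the month-6 and month-9 primary results have two possible meanings, and a single slope over months 0 to 9 does not separate them.

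*Protocol article*

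**What the plan says.** **Stopping.** The section Control arm/standard of care closes with "Intervention tactics will cease for both groups after the 3-month trial". It names both groups and states no exception.

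**Restarting.** The section The intervention, Patient level, describes what happens once the 3-month trial is over. Patients with a late refill, "uncontrolled BP or a missed appointment on two occasions at the standard 3-month clinic visit will be called by the nurse navigator". The resulting action plan may include restarting some PINGS components, with the examples "medication intake reminder alert via SMS delivery system reactivation, motivational messages". No counterpart for controls appears in the control-arm or follow-up sections.

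**Follow-up.** The Follow-up phase section says "Subjects in both arms of the study will be followed up for 6 months after the initial 3-month trial" and that "subjects will attend clinics monthly where their physicians will assess them clinically", with study assessments at months 3, 6 and 9.

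**Outcome and aim.** The abstract plans to "compare BP control at months 3, 6 and 9 as primary outcome measure", and no visit is singled out. The Background gives the aim as sustained BP control. The Discussion leaves only persistence beyond 9 months to a later trial.

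**Analysis.** Statistical analyses, Primary outcome measures, specifies a generalized linear mixed model (GLMM) with group, time (baseline, 3, 6, 9 months) and a time-by-intervention term. It also plans to estimate differences in proportions and in "average slopes between intervention versus control groups and evaluate linearity of trajectories", and to summarise each arm by a mean slope. Restarted components are not mentioned.

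**The concern.** The two statements about the period after month 3 lead to different estimands at two of the three primary time points. If the intervention stops, months 6 and 9 show how much of the effect survives withdrawal. If components can be switched back on, they show the result of a 3-month programme with optional restart for patients who are doing badly. Both are legitimate questions, but they support different conclusions about durability, and durability to month 9 is part of this trial's stated aim.

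Two features add to the difficulty. The restart is described for one arm only, and one of its triggers is the primary outcome itself. A month-9 difference reported as lasting benefit after withdrawal could therefore partly reflect renewed intervention. Separately, a straight-line slope from baseline to month 9 runs across the point at which the intervention ends. An effect that appears by month 3 and then holds, fades or is topped up is not linear, so one slope cannot report the month-3 effect and its persistence separately. The slopes are also meant to inform the analysis of the future trial.

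**Working it through.** The documents state no figure on this point that could be reproduced. The arm size used below is 2 physicians × 15 patients = 30, which agrees with the sample-size section (60 in total).

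**1. The two rules side by side**

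| | Control-arm section | Patient-level section |
|---|---|---|
| After month 3 | Tactics cease | Some components may restart |
| Who | Both groups | Intervention patients; no control counterpart described |
| Condition | None | Late refill, uncontrolled BP or missed appointment |
| What months 6 and 9 estimate | Persistence after withdrawal | PINGS plus optional restart |

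Month 3 has the same meaning under both rules, provided that any restart follows the month-3 visit.

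**2. How much a restart could matter (all rates assumed)**

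Let c be the proportion of intervention patients controlled at month 3, and r the proportion of the uncontrolled who become controlled because of a restart.

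- Patients who could meet the uncontrolled-BP trigger: 30 × (1 − c). For c = 0.40 this is 18; for c = 0.70 it is 9.
- Gain in intervention-arm control at months 6 and 9: (1 − c) × r × 100 points.
- Smallest case, c = 0.70 and r = 0.10: 0.30 × 0.10 × 100 = 3 points.
- Middle case, c = 0.50 and r = 0.25: 0.50 × 0.25 × 100 = 12.5 points.
- Largest case, c = 0.40 and r = 0.50: 0.60 × 0.50 × 100 = 30 points.

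These figures suppose that every uncontrolled patient is offered a restart. The protocol makes it optional, and the two-occasions condition may narrow the trigger, so actual numbers could be smaller.

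**3. What a slope over months 0 to 9 captures**

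For visits at 0, 3, 6 and 9 the mean is 4.5 and the sum of squared deviations is 20.25 + 2.25 + 2.25 + 20.25 = 45. The least-squares weights are (t − 4.5)/45, that is -0.100, -0.033, +0.033 and +0.100 per month. The month-3 difference thus has a small weight of opposite sign to those of months 6 and 9.

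Assumed SBP differences (intervention minus control) of 0, -15, -7.5 and d9 mmHg:

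slope = (-0.0333)(-15) + (0.0333)(-7.5) + 0.1 × d9 = 0.50 − 0.25 + 0.1 × d9 = 0.25 + 0.1 × d9 mmHg per month.

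- d9 = 0 gives +0.25, the wrong sign despite 15 mmHg of benefit at month 3.
- The slope is zero at d9 = -2.5. The sign is wrong only above that value, when more than 12.5/15 = 83% of the month-3 benefit has gone.
- With slower fading, 0, -15, -12, -10: 0.50 − 0.40 − 1.00 = -0.90, the right sign.

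Assumed differences in percent controlled (eligibility requires SBP of at least 140 mmHg, so the baseline difference is taken as 0):

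| Months 0, 3, 6, 9 | Pattern | Slope, points/month |
|---|---|---|
| 0, 30, 30, 30 | Early, fully kept | +3.0 |
| 0, 10, 20, 30 | One third of that month-3 effect, then rising | +3.3 |
| 0, 30, 15, 0 | Early, lost by month 9 | -0.5 |

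The first two patterns differ threefold at month 3 and have almost the same slope.

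**The case against.** The strongest reply is that the sections fit together: a restart presupposes a stop, so the plan is a default stop with an optional exception. On that reading months 6 and 9 estimate the whole strategy, and nothing is biased. This softens the conflict, but the control-arm sentence admits no exception, and neither the outcome nor the analysis section says that the strategy, restart included, is what months 6 and 9 estimate.

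A reader might infer that the month-6 and month-9 results are certainly biased upward. The documents do not support that. The restart is optional, its extent is unknown, and under the strategy reading there is no bias.

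The second reply is that slopes are not the main analysis. This largely stands. The GLMM includes time and a time-by-intervention term, differences in proportions are planned, and linearity will be evaluated. A reader might infer that the slope would generally reverse a real benefit; the working shows that this needs near-complete loss of effect by month 9.

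A reader might also see several primary visits and measures as a multiplicity failure. The outcomes are correlated, and the sample-size section rests on precision instead of testing, so a calculation of familywise error from independent tests does not fit this pilot.

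The two-occasions wording sits awkwardly beside monthly clinics. It could refer to the quarterly assessments, so it is an ambiguity to clear up and not a separate contradiction.

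**Conclusion.** The point holds as a matter of definition. The protocol gives two rules for the period after month 3, and two of the three primary time points change meaning with the rule. Month 3 is unaffected if restarts only follow that visit. The possible size at months 6 and 9, 3 to 30 points of intervention-arm control, rests entirely on assumed control and response rates and on restart being offered to all uncontrolled patients; it shows that the question is not negligible and is not a forecast. The slope issue is secondary: one slope cannot separate the month-3 effect from its persistence, but the planned model can supply what is needed.

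A reader might infer that month 3 must become the only primary time point. That does not follow. It would trade away the stated aim of sustained control, and months 6 and 9 are interpretable once their meaning is fixed. The correction should be made, because it decides what the trial may say about sustained control.

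**What to change.** 1. Reconcile the patient-level, control-arm and follow-up sections so that one rule describes the period after month 3 in each arm, and clarify the visits to which the trigger refers. No view is taken here on which rule is right.
2. State which effect months 6 and 9 estimate under that rule, and describe month 3 as the contrast that precedes any restart.
3. Record each restart by patient and date, and report the number by arm.
4. Make group differences at months 3, 6 and 9 with 95% CIs the main summary, taken from the planned GLMM with time as categorical. Keep the slope over months 0 to 9 as descriptive only.

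The cost is protocol wording and one log field. No additional patients, visits or measurements are needed.
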